### 2.4. General Procedure:

The study involves three cohorts of participants, each followed for six months, with weekly and monthly telephone check-ins and face-to-face visits at the three-month and six-month marks. These follow-ups are crucial for assessing the intervention’s effectiveness and making any necessary adjustments to the participants’ safety plans.

After enrollment, the app is installed on the participant’s phone, and a psychologist or psychiatrist assists in setting up the app. The participants in the intervention group will be taught how to use the safety plan. 

At the end of the six-month period, participants are assessed for changes in suicidal behavior and NSSIs. The follow-up also includes a review of the participants’ use of the app, their interaction with the safety plan and satisfaction with the intervention. Figure 1 illustrate the procedure. 

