### 2.7. Randomization and Follow-Up

A 1:1 randomization will take place after enrollment, where each participant will be assigned to one of the two groups. In both the control and intervention groups, an initial visit will take place during which a psychiatrist or psychologist will install the MEmind app on the participants’ mobile phone so that they can answer the questionnaires contained in the app with the guidance of the evaluator. In the case of self-administered questionnaires, the participants will answer directly on the screen of their mobile phone. In the case of hetero-administered questionnaires, the evaluator will complete them via the MEmind web portal, which is synchronized with the application.

Participants will be followed for six months, with weekly and monthly telephone visits and face-to-face visits at three and six months. In the intervention group, participants will also be given access to the safety plan included in the MEmind application. During the baseline visit, the plan will be set up for the first time and how it works will be explained. 

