### 2.8. Psychometric Assessment

The assessments will be carried out by a trained psychologist. The CSSRS [34] will be used to measure suicidal behavior and suicidal ideation. Sociodemographic data will also be collected, and a satisfaction survey will be carried out.

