### 2.11. Assessments: Questionnaires 

The assessments will be conducted by psychologists and/or psychiatrists, except for the screening in schools, which will be self-administered and carried out by the participant. All questionnaires will be completed in the MEmind collection portal, which allows for easy completion and immediate uploading to databases. 

The screening will consist of the completion of the following two short scales: Paykel Suicide Risk Scale [36];Inventory of Statements about Self-Injury scale (ISAS) [37].

The following questionnaires and instruments will be used for the assessment of items related to suicidal behavior and suicide ideation:Sociodemographic data including gender, age, family socioeconomic status, grade repetition, sexual orientation, number of siblings (including the participant) and child adoption.The Columbia Suicide Severity Rating Scale (CSSRS) [34] will be administered to measure suicide ideation and behavior. This scale will be employed both in the basal and the follow-up appointments.In addition, we will verify suicide attempts and suicide deaths through the digital medical record (clinical events).The Inventory for Depressive Symptomatology—Clinical (IDSC-30) scale [49] will be administered in order to measure depressive signs and symptoms.MacLean Screening Instrument for Borderline Personality Disorder [50].The Spanish version of the Death/Suicide Implicit Association Test (D/S-IAT) [38]Satisfaction surveys (one qualitative and one quantitative satisfaction survey).

The quantitative survey consists of the following questions, which participants will rate from 1 to 10:

1. Please rate your overall satisfaction with the application.

2. Is the application easy to use? 

3. Is the performance of the application good (speed of navigation, accuracy, lack of errors...)?

4. How do you rate the quality of the graphics?

5. How secure is the application with regard to the processing of personal data?

6. To what extent does the application have a clinical benefit? 

7. Would you be willing to recommend this application to family or friends?

The qualitative survey will ask the participant to comment on how their participation in the project has been, what aspect they liked most, what aspect they liked least and what suggestions they have for improvement, as well as any additional comments they may wish to make. 

Both surveys will be carried out at the six-month visit. 

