### 2.12. Assessment Criteria

After six months, a before-and-after comparison will be made in both the control and intervention groups. 

Our main outcome will be a reduction in suicidal behavior, as measured by a score on the CSSRS.

Our secondary outcomes will be as follows: The occurrence of suicidal behavior as a clinical event (completed suicide, attempted suicide, ED visit for suicidal ideation, ED visit for self-harm),Predictive validity of the D/S IAT and SI IAT tests to clinical events recorded during follow-up.Acceptability of the project through user-perceived satisfaction.Project feasibility measured by participation and retention.

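### The follow-ups that assess effectiveness are also used to adjust the safety plan, so the clinician rating the primary CSSRS is likely to know the arm

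*Protocol article*

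**What the plan says.** - **Purpose of the follow-ups (2.4).** The telephone contacts and the three- and six-month visits together serve to gauge "effectiveness and making any necessary adjustments to the" safety plans. In describing the end of the six months, the section says: "The follow-up also includes a review of the participants’ use of the app, their interaction with the safety plan and satisfaction with the intervention".
- **Who has a plan (2.7).** Only the intervention arm is given the safety plan. It is set up at the baseline visit.
- **Primary outcome (2.12).** "Our main outcome will be a reduction in suicidal behavior, as measured by a score on the CSSRS".
- **When it is measured (2.11).** "This scale will be employed both in the basal and the follow-up appointments".
- **Who measures it.** Section 2.8 says "The assessments will be carried out by a trained psychologist". Section 2.11 says "The assessments will be conducted by psychologists and/or psychiatrists, except for the screening in schools". Sections 2.4 and 2.7 name the same two professions for installing and setting up the app.
- **How clinician-administered scales are recorded (2.7).** "the evaluator will complete them via the MEmind web portal", which is linked to the app.
- **Limitations (section 3).** Dropout and baseline differences are discussed. Rater knowledge of the arm is not.

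**The concern.** Adjusting a plan, or reviewing how a participant has used it, reveals the arm, because controls have no plan. If the CSSRS is scored at the same appointment by someone who does that work or hears that conversation, the score is given with knowledge of the allocation. The CSSRS is rated in an interview, so a rater who expects the plan to help may probe or score slightly differently in the two arms.

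Participants cannot be masked to having a safety plan, but the rater's exposure can be reduced. A systematic rating difference does not shrink as the sample grows, while the smallest difference that reaches significance does. A pooled analysis of 1080 participants is therefore sensitive to a shift well below the effect the trial was planned around.

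**Working it through.** **Does the text bring rating and plan work together?**

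1. 2.4: effectiveness assessment and plan adjustment are purposes of one set of follow-ups.
2. 2.4: the six-month follow-up covers both outcome change and interaction with the plan.
3. 2.11 and 2.12: the CSSRS is the primary outcome and is given at follow-up appointments.
4. 2.7: only one arm has a plan to adjust or review.
5. 2.4, 2.7, 2.8 and 2.11: psychologists or psychiatrists set up the app, and psychologists or psychiatrists rate. No section separates these roles.

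Steps 1 to 4 are stated. That the rater knows the arm is an inference from all five.

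**The plan's own sample size figure (2.3).** Effect size 0.5, alpha 5%, power 95%, one-sample mean. By the exact noncentral t, the stated 45 per branch is reproduced one-sided (n = 45, power 0.951); the two-sided one-sample figure is 54. The 0.5 is thus a standardised effect in a one-sample setting, so setting an arm difference in SD beside it gives only a rough sense of scale.

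**What would a rating shift do?**

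Inputs from the article: 1:1 allocation (2.7); 1080 in total, so 1080 / 2 = 540 per arm (2.3); 60 per arm per centre (2.3); two-sided 5% (2.13).

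Assumptions: no true effect; a shift b of 0.10 or 0.20 SD in favour of the plan, the same at all centres; a two-sample t-test; and, for one scenario, 25% loss, giving 540 × 0.75 = 405 per arm.

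Probability of significance = P(|T| > t(0.975; 2n − 2)), where T is noncentral t with 2n − 2 degrees of freedom and noncentrality λ = b × √(n/2).

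| n per arm | critical t | λ, b = 0.10 | significant | λ, b = 0.20 | significant |
|---|---|---|---|---|---|
| 540 | 1.962 | 1.643 | 37.5% | 3.286 | 90.7% |
| 405 | 1.963 | 1.423 | 29.5% | 2.846 | 81.1% |
| 60 | 1.980 | 0.548 | 8.4% | 1.095 | 19.2% |

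With b = 0 every row gives 5%. With b = 0.05 the result is 13.0% at 540 per arm and 5.9% at 60.

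Smallest observed difference reaching p < 0.05: 1.962 × √(2/540) = 0.12 SD pooled, and 1.980 × √(2/60) = 0.36 SD in one centre.

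Against the planned 0.5: 0.10 / 0.5 = 20% and 0.20 / 0.5 = 40%.

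**The case against.** **The key step is inferred.** Section 2.4 speaks of the whole set of contacts. It does not say that every visit, or any one person, does both jobs, and it would read the same if a separate rater scored the CSSRS. A reader might infer that the rater built or adjusted the plan and so certainly knows the arm; the article does not support that. The sentence on the web portal describes where scores are entered at the initial visit, not what the evaluator sees later. This objection stands, and it limits the conclusion to likely knowledge.

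**Masking detail is often left to the full protocol.** This is true, and silence alone would be no finding. Here the article goes further and describes follow-ups that combine outcome assessment with work that reveals the arm. If roles are separated elsewhere, 2.4 still needs a sentence saying so.

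**The percentages rest on assumptions.** The shift has no source in the document. The calculation also uses a pooled between-arm t-test, whereas 2.12 describes a before-and-after comparison in each group and 2.13 names a Wilcoxon test for the CSSRS, with between-group t-tests given only for continuous variables in general. At the size planned for each centre the inflation is modest. All of this stands.

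**A masked rater is not a full cure.** Participants know their arm and may answer differently, so the remedy would not by itself restore a 5% error rate. This also stands.

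**Some mitigation is already planned.** Attempts and deaths are verified in the medical record (2.11), clinical events are a secondary outcome (2.12), and event curves are planned (2.13). These depend less on the rater, but they are not the primary outcome.

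**Conclusion.** The point holds in a limited form. The stated procedure places outcome assessment and plan adjustment in the same follow-ups, with plan review at six months, and describes no separation of roles. The clinician rating the primary CSSRS is therefore likely, but not certain, to know the arm.

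The tabulated percentages are conditional on the assumed shift, on no true effect and on the pooled two-sample comparison. A reader might take them as the trial's actual false-positive rate; the document gives no basis for that, because it says nothing about how far ratings would move. They show that a pooled analysis of this size could turn a shift of 20% to 40% of the planned effect into a significant result, while a single centre would be much less affected.

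**What to change.** State in 2.4 and 2.8 that, at the three- and six-month visits:

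1. the CSSRS is completed and locked before app use, satisfaction or the safety plan is discussed;
2. where a site has more than one trained rater, it is scored by existing staff who did not set up or adjust that participant's plan;
3. participants are asked not to mention the plan during the rating.

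Present the already planned record-verified events beside the CSSRS as a check less dependent on the rater. Add to section 3 that bias from unmasked participants remains.

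The cost is a short procedure note, scheduling effort and some loss of continuity between participant and rater. The article does not give the number of raters per site, so item 2 may not be possible everywhere; items 1 and 3 need no extra staff. Exchanging raters between sites by telephone is not suggested, because it would change the face-to-face format of these visits.

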### 2.5. Procedure: Clinical Setting

Once the recruitment period starts, the referring psychiatrist or psychologist will check the patient’s eligibility and explain the project in detail. If the patient shows interest, an interview will be held with their parents or guardians, who will read and sign the informed consent form. They will be given enough time to study the information sheet and any doubts they may have will be explained. They will also be told that participation is completely voluntary and that they can withdraw their consent at any time. If they wish, they can continue to use the application for free after having finished the study. 

### 2.6. Procedure: High School and University Setting

In the collaborating educational centers, the study will be explained and the informed consent will be obtained for the first phase of the study, which consists of a preliminary screening using the Paykel Suicide Risk Scale [37] and the Inventory of Statements about Self-Injury scale (ISAS) that assess NSSIs [38]. Students who have tested positive will be eligible to participate in the next phase of the study.

### 2.7. Randomization and Follow-Up

A 1:1 randomization will take place after enrollment, where each participant will be assigned to one of the two groups. In both the control and intervention groups, an initial visit will take place during which a psychiatrist or psychologist will install the MEmind app on the participants’ mobile phone so that they can answer the questionnaires contained in the app with the guidance of the evaluator. In the case of self-administered questionnaires, the participants will answer directly on the screen of their mobile phone. In the case of hetero-administered questionnaires, the evaluator will complete them via the MEmind web portal, which is synchronized with the application.

Participants will be followed for six months, with weekly and monthly telephone visits and face-to-face visits at three and six months. In the intervention group, participants will also be given access to the safety plan included in the MEmind application. During the baseline visit, the plan will be set up for the first time and how it works will be explained. 

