### 2.10. Ecological Momentary Assessment 

Digital monitoring will be carried out using the EMA methodology via the MEmind app. This app offers daily short questions that appear on the smartphone screen. Each day, a notification will appear with 2–4 random questions, which will appear at a random time during the day (from 9 a.m. to 9 p.m.) and which are part of a pool of 33 questions that make up the questionnaire. 

This questionnaire is based on the Salzburg Suicide Process Questionnaire (SSPQ) [41], the Patient Health Questionnaire-9 (PHQ-9) [42], the Positive and Negative Affect Schedule (PANA) [43], the Interpersonal Needs Questionnaire (INQ) [44], and previous EMA studies [45,46,47,48]. 

Questions will remain as a notification on the screen until they are answered. The application also has a free text field in which the participant can write comments on their status.

The EMA questions belong to six categories:Suicidality: 4 questions;Non-suicidal self-injury: 2 questions;Affect: 9 questions;Interpersonal experiences: 11 questions;Sleep: 4 questions;Apetite and eating: 3 questions.

The complete list of Ecological Momentary Assessment (EMA) questions can be found in Appendix A.

The digital safety plan is incorporated into the MEmind app and consists of a set of personalized coping strategies that the participant can use in the event of a suicidal crisis [20]. The original safety plan was designed by Stanley and Brown (2012) [20] and has been proven in several studies to decrease the risk of suicide [21]. 

It should be designed with the help of clinical staff. The safety plan will take advantage of smartphones by offering participants the ability to call loved ones, show relaxation videos, activate pre-recorded messages, link to websites with health resources, or connect the participant to emergency resources. During the first visit, the safety plan will be customized with the participant based on their personal preferences (e.g., by providing a list of emergency contacts or programming the app to trigger a song, image or video pre-selected by the participant).

The tabs of the safety plan are: 

The security plan consists of 7 tabs. In each tab, the patient can add text messages, voice messages, audios, photos, videos and links to websites.

The 7 tabs in the security plan are as follows:

1. Warning Signs—warning signs (thoughts, images, moods, situations, behaviors, etc.…) that may indicate a crisis is occurring.

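### As written, participants are randomised before the visit at which the baseline CSSRS is rated, and nothing stated keeps rater or participant unaware of the arm

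*Protocol article*

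**What the plan says.** All references are to the protocol article.

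- **Randomisation (section 2.7).** "A 1:1 randomization will take place after enrollment, where each participant will be assigned to one of the two groups".
- **Initial visit (section 2.7).** The next sentence begins "In both the control and intervention groups, an initial visit will take place during which a psychiatrist or psychologist will install the MEmind app". The stated purpose of installing the app is "so that they can answer the questionnaires contained in the app with the guidance of the evaluator".
- **Rater-completed scales (section 2.7).** "In the case of hetero-administered questionnaires, the evaluator will complete them via the MEmind web portal".
- **Safety plan (sections 2.7 and 2.10).** For the intervention arm, "During the baseline visit, the plan will be set up for the first time and how it works will be explained". Section 2.10 agrees: "During the first visit, the safety plan will be customized with the participant based on their personal preferences".
- **CSSRS schedule (section 2.11).** "This scale will be employed both in the basal and the follow-up appointments".
- **Primary outcome and test (sections 2.12 and 2.13).** The main outcome is a reduction in suicidal behaviour by CSSRS score. It is judged by a before-after comparison in each group, with a Wilcoxon test of baseline against end of follow-up.
- **Follow-up contacts (section 2.4).** They have two purposes, assessing the intervention's "effectiveness and making any necessary adjustments to the participants", where the phrase goes on to name their safety plans.
- **Safeguards (section 3).** Covariance analysis for baseline differences, and intention-to-treat analysis.

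**The concern.** A baseline is useful in a randomised comparison because allocation cannot have influenced it. Here the text puts assignment first and the baseline rating second. The rating is also made at a visit whose content differs by arm: one arm builds a safety plan with clinical staff and the other does not.

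The CSSRS is rated by a psychologist or psychiatrist, so judgement enters the score. If either party knows the arm, the rating or the answers may shift. The primary measure is a before-after change, so such a shift would appear as change over six months even if the six-month scores were identical in the two arms. It could run either way. A higher baseline rating in the intervention arm would inflate the apparent reduction. A lower one, for instance because the participant has just worked through the plan, would hide a real effect.

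**Working it through.** **Step 1: order of events.** Set side by side, the sections give this sequence.

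1. Educational cohorts only: Paykel and ISAS screening (section 2.6). Neither is the primary measure. Section 2.5 describes no scale before enrolment in the clinical cohort.
2. Enrolment.
3. Assignment to one of two groups (section 2.7).
4. Initial visit in both groups: app installed and questionnaires answered, with rater-administered scales entered by the evaluator (section 2.7). The CSSRS belongs to this appointment (section 2.11).
5. At the same visit, intervention arm only: the safety plan is set up and customised (sections 2.7 and 2.10).

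Section 2.4 says that the app is installed after enrolment. That fits this sequence and does not reverse steps 3 and 4. No section describes a masked rater, or a rule that the CSSRS is scored before allocation is disclosed.

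**Step 2: how a shift would carry through.** The plan gives no figure on this point. Its minimum of 45 per branch (section 2.3) reproduces as a one-sided, one-sample t test with effect size 0.5 (power 0.951), but does not enter here. The only inputs taken from the plan are 60 per arm in one centre and 60 × 9 = 540 per arm overall.

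Assume no true effect, a common SD of 1 at both times, correlation rho between baseline and six months, and a shift of b SD in one arm's baseline rating that leaves the six-month score untouched.

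- Between-arm comparison of change: bias = b; standard error = √(2(1 − rho) × 2/n).
- Baseline-adjusted comparison (ANCOVA): bias = rho × b; standard error = √((1 − rho²) × 2/n).
- Rejection probability, two-sided 5%, normal approximation: Φ(bias/SE − 1.96) + Φ(−bias/SE − 1.96).

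Worked case with n = 60, rho = 0.5, b = 0.2:

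- Change: SE = √(2 × 0.5 × 2/60) = 0.183; 0.2/0.183 = 1.095; rejection probability 0.195.
- ANCOVA: bias = 0.5 × 0.2 = 0.10; SE = √(0.75 × 2/60) = 0.158; 0.10/0.158 = 0.632; rejection probability 0.097.

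False-positive rate over an assumed range (b from 0.1 to 0.3, rho from 0.3 to 0.7):

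| Per arm | Comparison | b = 0.1, rho = 0.3 | b = 0.2, rho = 0.5 | b = 0.3, rho = 0.7 |
|---|---|---|---|---|
| 60 | change | 0.075 | 0.195 | 0.564 |
| 60 | ANCOVA | 0.053 | 0.097 | 0.364 |
| 540 | change | 0.284 | 0.908 | >0.999 |
| 540 | ANCOVA | 0.081 | 0.475 | 0.998 |

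With the baseline fixed before allocation, b = 0 and the rate is 0.05 throughout. The values of b and rho are assumptions with no source in the article. The table shows the mechanism, that adjustment reduces the bias without removing it, and that a larger trial does not dilute it. It does not estimate what will happen in this trial.

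**Step 3: the stated safeguards.** Covariance analysis would use a covariate that is itself measured after randomisation, so rho × b remains. Intention-to-treat governs who is analysed, not how the baseline was rated.

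**The case against.** The strongest reply is that the text never says when allocation is disclosed, or whether the CSSRS precedes plan set-up within the visit. The sentence about both groups may mean only that both arms receive the visit. Section 2.7 describes the questionnaires in one paragraph and plan access in the next, which fits assessing first and intervening second. Figure 1, whose image was not available to me, may show the order, and a journal article commonly leaves the running order of a visit to the full protocol.

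Much of this stands. A reader might infer that the baseline is in fact scored with the arm known; the document does not establish that. It is a reasonable inference only because assignment comes first, staff build the plan at the same visit, and no masking is described. A reader might also infer that people who leave on learning their arm drop out of the paired analysis for want of a baseline. That presumes disclosure before the visit, which no section states. Nor can a size be put on the bias: expressing an assumed shift as a share of a detectable effect would need a shift and a correlation that the article does not give.

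What does not stand is treating this as mere missing detail. The order of randomisation and initial visit is stated, nothing in section 2.4 reverses it, and it is the less protective order.

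Whether follow-up ratings are masked is a separate question and adds no weight to the point about baseline timing.

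**Conclusion.** The point holds as one about stated order. As section 2.7 is written, randomisation precedes the visit at which the baseline CSSRS is rated and, in the intervention arm, the safety plan is set up. Nothing stated keeps rater or participant unaware of the arm at that rating. Because the primary outcome is a before-after CSSRS comparison, any arm-related shift in the baseline would enter the change score, and covariance adjustment would remove only part of it.

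The document does not support a claim that bias is present, or any figure for its size or direction. The conclusion rests on reading section 2.7 in sequence and on the absence of a masking statement in the article. If sites already score the baseline before allocation is known, the remedy is a sentence of clarification; if they do not, it is a change of procedure worth making.

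**What to change.** Reorder section 2.7 as follows:

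1. Consent and app installation.
2. All baseline measures (CSSRS, IATs, IDSC-30) completed and locked.
3. The participant is randomised, or the allocation is released.
4. Only then is the safety plan opened and customised for the intervention arm.

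At three and six months, state that the CSSRS is completed before any discussion of the safety plan.

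**Cost.** This needs no additional visit and no change in sample size. The small downside is that allocation must be available during the visit, once the baseline is locked. The article describes the MEmind portal as a data-collection system and does not say whether it can lock forms, so that should be checked.
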